## Abstract

Manual wheelchair users are at high risk of upper limb overuse injuries due to repetitive propulsion mechanics. To address this, we developed a novel detachable push–pull dual-propulsion device that enables both forward and backward propulsion, aiming to reduce shoulder strain and promote balanced muscle engagement. This study presents a protocol to evaluate the device’s biomechanical impact and ergonomic effects, focusing on objective, quantitative analysis using a repeated-measures within-subject design. Thirty participants with spinal cord injury will perform standardized propulsion trials under two conditions: push and pull. Motion capture and surface electromyography (EMG) will assess upper limb kinematics and muscle activation. Each propulsion mode will be repeated over a 10-m track, and maximum voluntary contraction (MVC) data will be collected for EMG normalization. The protocol aims to provide objective evidence on the propulsion efficiency, muscle distribution, and ergonomic safety of the device. Findings will inform future assistive technology development and rehabilitation guidelines for manual wheelchair users.

## 1. Introduction

Manual wheelchair propulsion imposes significant physical demands on the upper limbs, frequently resulting in chronic shoulder pain, muscular imbalances, and overuse injuries, particularly among individuals with spinal cord injury (SCI) [1,2,3]. The repetitive nature of traditional forward propulsion exacerbates the risk of secondary musculoskeletal complications, which can adversely affect users’ quality of life and functional independence [4,5]. These cumulative risks highlight the pressing need for innovative propulsion solutions that can alleviate upper limb stress without compromising independent mobility.

Various alternative propulsion mechanisms have been explored to mitigate these issues and improve propulsion efficiency. Lever-based wheelchair propulsion, for instance, has demonstrated benefits such as altering muscle activation patterns, reducing peak muscular loads, and redistributing muscular demands [6]. le Rütte et al., (2022) showed that a push–pull lever mechanism significantly reduced peak propulsion forces and energy expenditure compared to conventional hand rim propulsion, highlighting its ergonomic advantages [7]. Furthermore, recent research on reverse propulsion has shown significant reductions in superior and posterior shoulder forces [8,9,10], highlighting the importance of propulsion direction on upper limb biomechanics and muscle activity [11] compared to traditional propulsion methods.

Building upon these findings, our research team has developed a novel detachable push–pull dual-propulsion device designed to integrate the biomechanical advantages of pushing and pulling methods, facilitating easy attachment to and detachment from conventional manual wheelchairs. This newly developed device is anticipated to enhance propulsion efficiency, reduce shoulder loading, and promote balanced muscle activation patterns compared to traditional propulsion methods. Moreover, its detachable design enables integration with standard wheelchairs, allowing for broader usability without structural modification. These anticipated benefits require objective verification through the biomechanical evaluation protocol presented in this study.

However, a comprehensive and rigorous usability assessment protocol is essential before implementing it more broadly. Current usability assessment protocols commonly integrate multimodal biomechanical measurements, including kinematic motion analysis, electromyography (EMG), and kinetic analysis. Bontrager et al., (2008), for example, utilized EMG to assess shoulder muscle loads, while Kukla et al., (2022) combined 3D motion analysis and EMG to evaluate the biomechanical impacts of innovative wheelchair propulsion mechanisms [6,12]. Recent studies have emphasized the importance of integrating objective performance-based metrics in assistive device evaluation, particularly through synchronized biomechanical measurements such as motion capture and EMG [13]. Despite such advances, few studies have employed rigorous, standardized protocols to examine dual-mode propulsion in realistic propulsion scenarios.

Thus, this study proposes a structured protocol for comprehensively assessing the usability of the novel detachable push–pull dual-propulsion device. This protocol integrates biomechanical analyses, including kinematic motion capture and electromyography (EMG), to rigorously evaluate the effects of propulsion methods on upper limb load, muscle activity, and propulsion efficiency. The protocol also aims to establish baseline biomechanical profiles that may inform both device refinement and clinical decision-making for safe and effective wheelchair propulsion. Focusing on biomechanical efficiency, this protocol aims to generate evidence-based insights that can inform future wheelchair design and clinical recommendations to enhance the health and functional mobility of manual wheelchair users. Ultimately, these findings could support evidence-based rehabilitation strategies and contribute to the design of future assistive technologies tailored to user-specific biomechanical needs.

## 2. Materials and Methods

### 2.1. Participants

A total of 30 adults diagnosed with SCI will be recruited for this study. The inclusion criteria will be as follows: participants will be adults between the ages of 20 and 60 years who will have been diagnosed with spinal cord injury (SCI). They must have used a manual wheelchair regularly for at least six months and will be required to have the ability to propel a wheelchair independently over a 10-m track. Additionally, participants must not have any acute or chronic impairments affecting their upper limbs and will need to provide written informed consent before participation.

The exclusion criteria will be defined as follows: individuals will be excluded if they have neurological conditions other than SCI, current upper limb fractures, clinically diagnosed shoulder pathology, or other musculoskeletal disorders that could interfere with propulsion. Further exclusion criteria will include active shoulder pain, cognitive impairments that limit comprehension of study instructions, and prior participation in competitive wheelchair sports or structured upper limb training programs within the past six months. Any additional medical condition identified by the research team as potentially compromising participant safety or data integrity will also result in exclusion.

Before enrollment, all participants will receive detailed information about the study’s purpose, procedures, risks, and benefits, and written informed consent will be obtained.

### 2.2. Study Design

This study will employ a repeated-measures within-subject design to evaluate the usability and biomechanical effects of a detachable push–pull dual-propulsion device developed for manual wheelchair users. Each participant will perform wheelchair propulsion tasks under two specific experimental conditions: (1) forward propulsion using the traditional handrim method (standard manual wheelchair), and (2) backward propulsion using the dual-propulsion device (pull mode). To enhance clarity, a schematic illustration (Figure 1) will be provided to visually depict the two experimental conditions: push propulsion using a handrim and pull propulsion using the dual-propulsion device. The arrows in the figure will indicate the direction of propulsion and the rotation of the wheels.

These two propulsion strategies will be selected to distinguish the mechanical and physiological differences between conventional pushing and the novel pulling movements using the developed device. This within-subject comparison will enable the evaluation of the dual-propulsion system in relation to standard propulsion, with a focus on biomechanics and usability.

While this study will adopt a within-subject repeated-measures design to compare two propulsion modes, we acknowledge the absence of a separate control group as a limitation. In future randomized controlled trials, we plan to include a conventional propulsion-only control group to improve external validity and control for potential confounding variables.

The order of propulsion conditions will be randomized for each participant to minimize potential learning effects, fatigue accumulation, and sequence bias. Prior to data collection, all participants will receive standardized instructions and practice sessions on the use of the propulsion device and experimental procedures to ensure sufficient familiarity.

All experiments will be conducted in a controlled laboratory setting. The primary outcome measures will include kinematic data obtained from 3D motion analysis and electromyographic (EMG) signals collected from upper limb muscles. Adequate rest intervals will be provided between conditions to prevent muscular fatigue and maintain the accuracy of the data.

This study protocol was reviewed and approved by the Institutional Review Board of the National Rehabilitation Center (Approval No. NRC-2024-04-018). It was designed in accordance with the SPIRIT 2013 guidelines (Standard Protocol Items: Recommendations for Interventional Trials) [14]. A flowchart will illustrate the sequential steps of the experimental protocol (Figure 2), including participant recruitment, familiarization with the propulsion device, randomized push and pull trials along a 10-m track, and synchronized collection of kinematic and electromyographic (EMG) data. Maximum voluntary contraction (MVC) values will be recorded post-trial for EMG normalization.

The primary hypothesis of this study is that the pull-mode propulsion using the dual-propulsion device will result in more balanced upper limb muscle activation and reduced shoulder loading compared to standard push-mode propulsion.

### 2.3. Dual-Propulsion Device

The detachable push–pull propulsion device is engineered to be mounted on a standard manual wheelchair frame via a secure locking mechanism. It allows users to switch between traditional push propulsion and a novel pull-based mode using a detachable lever-arm structure designed for efficient biomechanical engagement. The system is compatible with standard active-type wheelchairs, enabling users to alternate propulsion strategies based on individual needs or task demands.

Figure 3 provides a side view of the key structural components of the detachable two-way propulsion system. The figure illustrates the pushrim, the detachable mechanical unit for bidirectional propulsion, and its integration with a standard manual wheelchair wheel. This figure will help visualize how the device is mounted and how the propulsion interface is layered over the existing wheel structure.

The dual-propulsion device used in this study is a detachable bidirectional propulsion mechanism that enables both forward (push) and backward (pull) propulsion for manual wheelchair users. This device was developed to reduce upper limb overuse by engaging different muscle groups depending on the direction of propulsion, thereby inducing biomechanical variation and offering ergonomic benefits to the user [15].

The system consists of a central drive module mounted to the wheelchair frame and a pair of rotating levers attached to each rear wheel. These levers are connected through a gear-based linkage system that transmits power to the wheels during both pushing and pulling actions. A mode-switching mechanism, operated via a lever or switch, allows the user to intuitively alternate propulsion directions.

To ensure independent use and safety, the device includes a locking mechanism to secure the stationary levers and a quick-release system for easy attachment and detachment. This design permits installation without requiring structural modification to the existing wheelchair. The device is compatible with most active-type manual wheelchairs, and the prototype used in this study was based on the Nissin NA-430 model (Figure 4).

The handles and gear mechanism are optimized for user comfort and mechanical efficiency. The device’s total weight is approximately 3.6 kg, and its addition to the wheelchair does not significantly increase the overall width, thus maintaining maneuverability in daily activities. This study will validate the device’s biomechanical effects and propulsion efficiency using a structured experimental protocol.

The detachable push–pull dual-propulsion device includes a secure clamp-lock mechanism that attaches to standard wheelchair frames. Stability is ensured through a dual-locking gear system that prevents unintentional disengagement. Load-bearing components are constructed from lightweight aluminum alloy tested according to ISO 7176 [16] durability standards, and the lever mechanism features an anti-rebound damper to avoid sudden backward motions.

### 2.4. Experimental Protocol

This study will employ a repeated-measures within-subject design to evaluate the propulsion efficiency and biomechanical characteristics of a detachable push–pull dual-propulsion device developed for manual wheelchair users. The experiment will be conducted in a controlled laboratory setting at the National Rehabilitation Center, where each participant will perform two propulsion conditions: (1) forward (push) propulsion and (2) backward (pull) propulsion. Each condition will be repeated five times, resulting in ten trials of propulsion per participant. The order of the conditions will be randomized for each individual to minimize potential learning or fatigue effects.

The experimental session will consist of several sequential phases, including informed consent, familiarization, propulsion trials (push and pull), rest periods, and MVC measurements. A structured participant timeline will be followed to ensure procedural consistency across subjects, as outlined in Table 1. Each propulsion condition will be completed five times over a 10-m track, with adequate rest provided between trials. After the propulsion trials, maximum voluntary contraction (MVC) values will be collected for EMG normalization.

The experiment will take place along a 10-m straight indoor track. Before data collection, participants will receive a 3-minute familiarization session with the wheelchair equipped with the dual-propulsion device. During this time, participants will be instructed on how to operate the device and perform the experimental tasks. Adequate rest periods will be ensured throughout the protocol to minimize muscular fatigue. Upon completion of all propulsion tasks, MVC measurements will be obtained for each targeted muscle group, with each MVC performed three times for three seconds per trial.

Upper limb kinematic data and electromyographic (EMG) signals will be recorded during the propulsion tasks. Three-dimensional motion analysis will be conducted using the VICON system (Oxford, UK) with 10 fixed cameras. Reflective markers will be placed at anatomical landmarks to enable precise tracking of shoulder and elbow joint angles and movement trajectories. Surface EMG data will be collected using the Trigno Wireless EMG System (Delsys Inc., Natick, MA, USA), targeting 10 upper limb muscles on the dominant side. Electrodes will be positioned according to SENIAM guidelines, except where alternative validated placements are used. All data will be synchronized and processed using Visual 3D software (version 6.0, C-Motion, Germantown, MD, USA).

This experimental design aims to quantitatively assess differences in muscle activation, joint motion, and propulsion dynamics between forward and backward propulsion and to objectively evaluate the usability and biomechanical advantages of the proposed dual-propulsion device.

Table 1 outlines the sequential phases of the experimental session, including pre-test procedures (consent and demographics), device familiarization, propulsion trials using push and pull modes, designated rest intervals, and post-test MVC measurements for EMG normalization. Each propulsion condition was performed five times over a 10-m track, with synchronized kinematic and EMG recordings.

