### 2.7. Data Analysis

All collected data will be analyzed using SPSS Statistics software (version 26.0, IBM Corp., Armonk, NY, USA). Descriptive statistics (mean ± standard deviation) will be used to summarize participant characteristics and all outcome measures.

To assess the normality of the data distribution, the Shapiro–Wilk test will be conducted. Based on these results, either parametric or non-parametric tests will be used. For normally distributed data, repeated-measures analysis of variance (ANOVA) will be conducted to compare biomechanical parameters (e.g., joint angles, ROM, iEMG, RMS values) between the two propulsion modes (push vs. pull). Mauchly’s test will be performed to assess the assumption of sphericity, and if violated, the Greenhouse–Geisser correction will be applied. Signals will be sampled at 2000 Hz.

For non-normally distributed variables, the Wilcoxon signed-rank test will be applied. All statistical analyses will adopt a two-tailed significance level of *p* < 0.05. To assess the magnitude of differences between conditions, effect sizes will be reported (Cohen’s d or partial eta squared, as appropriate).

Additionally, kinematic variables such as shoulder flexion and extension angles, as well as stroke cadence, will be calculated over complete propulsion cycles. EMG signals will be band-pass filtered (20–450 Hz), full-wave rectified, and smoothed using the root mean square (RMS) method with a 100-ms moving window. Integrated EMG (iEMG) data will also be computed to capture the total muscle activation over each propulsion cycle. EMG data will be normalized to maximum voluntary contraction (%MVC). Comparisons of muscle activity patterns will be made across propulsion modes to evaluate biomechanical efficiency, with a focus on reduced activation in shoulder prime movers during the pull phase.

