**Figure 4 life-15-01037-f004:**
[figure not shown]
Prototype of the detachable push–pull dual-propulsion device mounted on a manual wheelchair [15]. The system comprises lever arms, gear mechanisms, and a central mounting module that is compatible with standard wheelchair frames. The red circle shows the quick-release axles as applied in the two-way propulsion system. Scale bar = 15 cm.

**Table 1 life-15-01037-t001:** Participant timeline and procedures.

Phase	T0: Pre-Test	T1: Familiarization	T2: Push Trials	T3: Rest	T4: Pull Trials	T5: Post-Test (MVC)
Consent and Demographics	✔️					
Device Instruction		✔️				
Practice (3 min)		✔️				
Kinematic Recording			✔️ (5 × 10 m)		✔️ (5 × 10 m)	
EMG Recording			✔️		✔️	✔️ (3 reps × 3 s)
Rest Interval (≥5 min)				✔️		

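### Table 1 shows push before pull as the timeline for everyone, while the text randomises the order; the two must be reconciled, because a fixed order would alias propulsion mode with period

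*Protocol article*

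**What the plan says.** The text of the protocol article randomises the order in three places.

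- Section 2.2: "The order of propulsion conditions will be randomized for each participant to minimize potential learning effects, fatigue accumulation, and sequence bias".
- Section 2.2, describing the flowchart: "randomized push and pull trials along a 10-m track".
- Section 2.4: "The order of the conditions will be randomized for each individual to minimize potential learning or fatigue effects".

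Section 2.4 also makes Table 1 the working timeline: "A structured participant timeline will be followed to ensure procedural consistency across subjects, as outlined in Table 1". It later adds that "Table 1 outlines the sequential phases of the experimental session". The column headings of Table 1 run from pre-test and familiarisation to "T2: Push Trials", then rest, then "T4: Pull Trials", then the MVC measurements. The table shows no alternative order and has no note that the two propulsion columns are exchangeable.

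Section 2.7 says that "repeated-measures analysis of variance (ANOVA) will be conducted to compare biomechanical parameters" between push and pull, with the Wilcoxon signed-rank test for non-normal variables. It names no period or sequence factor.

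**The concern.** The article gives laboratory staff two incompatible instructions on the order of the conditions. The columns of Table 1 are labelled in time order, and the other columns follow the sequence that the text requires: consent first, then practice, with MVC last. A member of staff could therefore reasonably read the push and pull columns in the same way.

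Push against pull is the only comparison in the study. If pull always came second, any practice, warm-up or fatigue effect would enter the pull-minus-push difference in full. The protocol itself treats such effects as credible, since they are its stated reason for randomising. Data collected in a fixed order could not be repaired afterwards.

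**Working it through.** The article states no power or error figure on this point, so there is none to reproduce.

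**Inputs from the article.** 30 participants (section 2.1); two conditions per participant (sections 2.2 and 2.4); two-sided 5% level (section 2.7). With two levels, the repeated-measures ANOVA is equivalent to a paired t-test.

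**Assumed input.** The period effect d, in units of the SD of the within-participant difference. The article gives no value, so a range is used.

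**Set-up.** Let D be pull minus push for one participant, δ the true mode effect and d the period effect (second position minus first). Then the expected D is δ + s·d, where s = +1 if pull comes second and s = −1 if pull comes first.

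**Case 1: Table 1 followed literally.** Every s is +1.

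1. Separability: with columns for intercept, mode and period, a push row is (1, 0, 0) and a pull row is (1, 1, 1). The mode and period columns are identical, so the rank is 2 of 3. A period term could not be estimated apart from mode.
2. False positives when δ = 0: the test statistic is non-central t with 29 degrees of freedom and non-centrality d·√30, where √30 = 5.477.

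| Assumed d | d·√30 | False-positive rate |
|---|---|---|
| 0.1 | 0.548 | 0.083 |
| 0.2 | 1.095 | 0.185 |
| 0.3 | 1.643 | 0.356 |
| 0.5 | 2.739 | 0.754 |

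**Case 2: order randomised as the text says, no period term.**

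1. Both sequences occur, the design has rank 3 of 3, and mode and period are separable.
2. The mean of s is zero in expectation, so the expected bias is zero. Under simple randomisation its SD is 1/√30 = 0.18. A single trial could therefore carry about 18% of the period effect (1 SD) by chance, and the test allows for this.
3. Simulated type I error (100,000 runs per setting) for d = 0.2, 0.5 and 0.8 is 0.049, 0.049 and 0.050 under simple randomisation. Under a 15:15 split it is 0.045, 0.028 and 0.012. None exceeds 5%. The 15:15 values fall below it because the unmodelled period effect inflates the SD of D; at d = 0.5 the factor is about √(1 + 0.5²) = 1.118.
4. Simulated power for a true mode effect of 0.5 SD, 15:15 split:

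| Assumed d | Without period term | With period term |
|---|---|---|
| 0.2 | 0.74 | 0.75 |
| 0.5 | 0.67 | 0.75 |
| 0.8 | 0.55 | 0.75 |

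**The case against.** The strongest reply is that Table 1 is only a schematic with one order drawn for illustration. Three explicit statements randomise the order, and one of them is in section 2.4, shortly before the reference to Table 1. Against them stand two column headings. This is a plausible account of what was meant. It does not remove the contradiction, because the table is not marked as illustrative and the text says that it will be followed for all participants.

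A reader might infer that the trial is confounded as planned. The documents do not support that: confounding follows only if the fixed order of Table 1 is carried out.

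A reader might also infer that the missing order term causes the confounding. It does not. Under a fixed order the term could not help, and under a randomised order its absence gives no expected bias and no inflated type I error.

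Two further objections stand. Model terms and the method of generating the sequence are commonly left to an analysis plan or full protocol that is not shown, so their absence from an article is not an error. The period effects are assumed, and the article has features that may keep them small: at least 5 minutes of rest between conditions, a 3-minute familiarisation, at least six months of regular wheelchair use, and only ten 10-m runs. These features may reduce period effects but do not rule them out.

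**Conclusion.** The point holds as an internal contradiction with a conditional consequence. Table 1 and the randomisation statements cannot both be followed for a participant allocated pull first.

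If Table 1 were followed, mode and period would be inseparable, and a modest period effect would be enough to mislead: at an assumed 0.2 SD the false-positive rate is about 19%, and at 0.5 SD about 75%. These figures rest on 30 complete pairs, normally distributed differences and the assumed period effects.

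If the text is followed, the comparison is valid as it stands. The remaining issue is precision, for example power of 0.67 instead of 0.75 at an assumed 0.5 SD period effect with a 15:15 split. Reconciling Table 1 is therefore necessary before data collection; the period term is a recommendation.

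**What to change.** **Necessary.** Relabel T2 in Table 1 as *First condition (push or pull, as allocated)* and T4 as *Second condition*. The cost is two column headings.

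**Secondary.** In the parametric comparison, fit mode + period + participant. This costs one degree of freedom (29 to 28) and recovers the precision that a period effect would otherwise take. The Wilcoxon route is not covered by this change.

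**Optional.** Use a balanced sequence list with 15 participants starting in each mode, so that a period effect cancels exactly in the mode contrast if all 30 provide data. The full protocol may already provide for this.
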